## Abstract

**Background:**

The disruption of health and medical education by the COVID-19 pandemic made educators question the effect of online setting on students’ learning, motivation, self-efficacy and preference. In light of the health care staff shortage online scalable education seemed relevant. Reviews on the effect of online medical education called for high quality RCTs, which are increasingly relevant with rapid technological development and widespread adaption of online learning in universities. The objective of this trial is to compare standardized and feasible outcomes of an online and an onsite setting of a research course regarding the efficacy for PhD students within health and medical sciences: Primarily on learning of research methodology and secondly on preference, motivation, self-efficacy on short term and academic achievements on long term. Based on the authors experience with conducting courses during the pandemic, the hypothesis is that student preferred onsite setting is different to online setting.

**Methods:**

Cluster randomized trial with two parallel groups. Two PhD research training courses at the University of Copenhagen are randomized to online (Zoom) or onsite (The Parker Institute, Denmark) setting. Enrolled students are invited to participate in the study. Primary outcome is short term learning. Secondary outcomes are short term preference, motivation, self-efficacy, and long-term academic achievements. Standardized, reproducible and feasible outcomes will be measured by tailor made multiple choice questionnaires, evaluation survey, frequently used Intrinsic Motivation Inventory, Single Item Self-Efficacy Question, and Google Scholar publication data. Sample size is calculated to 20 clusters and courses are randomized by a computer random number generator. Statistical analyses will be performed blinded by an external statistical expert.

**Discussion:**

Primary outcome and secondary significant outcomes will be compared and contrasted with relevant literature. Limitations include geographical setting; bias include lack of blinding and strengths are robust assessment methods in a well-established conceptual framework. Generalizability to PhD education in other disciplines is high. Results of this study will both have implications for students and educators involved in research training courses in health and medical education and for the patients who ultimately benefits from this training.

**Trial registration:**

Retrospectively registered at ClinicalTrials.gov: NCT05736627. SPIRIT guidelines are followed.

**Supplementary Information:**

The online version contains supplementary material available at 10.1186/s12909-024-05915-z.

## Background

Medical education was utterly disrupted for two years by the COVID-19 pandemic. In the midst of rearranging courses and adapting to online platforms we, with lecturers and course managers around the globe, wondered what the conversion to online setting did to students’ learning, motivation and self-efficacy [1–3]. What the long-term consequences would be [4] and if scalable online medical education should play a greater role in the future [5] seemed relevant and appealing questions in a time when health care professionals are in demand. Our experience of performing research training during the pandemic was that although PhD students were grateful for courses being available, they found it difficult to concentrate related to the long screen hours. We sensed that most students preferred an onsite setting and perceived online courses a temporary and inferior necessity. The question is if this impacted their learning?

Since the common use of the internet in medical education, systematic reviews have sought to answer if there is a difference in learning effect when taught online compared to onsite. Although authors conclude that online learning may be equivalent to onsite in effect, they agree that studies are heterogeneous and small [6, 7], with low quality of the evidence [8, 9]. They therefore call for more robust and adequately powered high-quality RCTs to confirm their findings and suggest that students’ preferences in online learning should be investigated [7–9].

This uncovers two knowledge gaps: I) High-quality RCTs on online versus onsite learning in health and medical education and II) Studies on students’ preferences in online learning.

Recently solid RCTs have been performed on the topic of web-based theoretical learning of research methods among health professionals [10, 11]. However, these studies are on asynchronous courses among medical or master students with short term outcomes.

This uncovers three additional knowledge gaps: III) Studies on synchronous online learning IV) among PhD students of health and medical education V) with long term measurement of outcomes.

The rapid technological development including artificial intelligence (AI) and widespread adaption as well as application of online learning forced by the pandemic, has made online learning well-established. It represents high resolution live synchronic settings which is available on a variety of platforms with integrated AI and options for interaction with and among students, chat and break out rooms, and exterior digital tools for teachers [12–14]. Thus, investigating online learning today may be quite different than before the pandemic. On one hand, it could seem plausible that this technological development would make a difference in favour of online learning which could not be found in previous reviews of the evidence. On the other hand, the personal face-to-face interaction during onsite learning may still be more beneficial for the learning process and combined with our experience of students finding it difficult to concentrate when online during the pandemic we hypothesize that outcomes of the onsite setting are different from the online setting.

To support a robust study, we design it as a cluster randomized trial. Moreover, we use the well-established and widely used Kirkpatrick’s conceptual framework for evaluating learning as a lens to assess our outcomes [15]. Thus, to fill the above-mentioned knowledge gaps, the objective of this trial is to compare a synchronous online and an in-person onsite setting of a research course regarding the efficacy for PhD students within the health and medical sciences:Primarily on theoretical learning of research methodology andSecondly on◦ Preference, motivation, self-efficacy on short term◦ Academic achievements on long term

## Methods

### Trial design

This study protocol covers synchronous online and in-person onsite setting of research courses testing the efficacy for PhD students. It is a two parallel arms cluster randomized trial (Fig. 1).

**Fig. 1 Fig1:**
[figure not shown]
Consort flow diagram

The study measures baseline and post intervention. Baseline variables and knowledge scores are obtained at the first day of the course, post intervention measurement is obtained the last day of the course (short term) and monthly for 24 months (long term).

Randomization is stratified giving 1:1 allocation ratio of the courses. As the number of participants within each course might differ, the allocation ratio of participants in the study will not fully be equal and 1:1 balanced.

### Study setting

The study site is The Parker Institute at Bispebjerg and Frederiksberg Hospital, University of Copenhagen, Denmark. From here the courses are organized and run online and onsite. The course programs and time schedules, the learning objective, the course management, the lecturers, and the delivery are identical in the two settings. The teachers use the same introductory presentations followed by training in break out groups, feed-back and discussions. For the online group, the setting is organized as meetings in the online collaboration tool Zoom® [16] using the basic available technicalities such as screen sharing, chat function for comments, and breakout rooms and other basics digital tools if preferred. The online version of the course is synchronous with live education and interaction. For the onsite group, the setting is the physical classroom at the learning facilities at the Parker Institute. Coffee and tea as well as simple sandwiches and bottles of water, which facilitate sociality, are available at the onsite setting. The participants in the online setting must get their food and drink by themselves, but online sociality is made possible by not closing down the online room during the breaks. The research methodology courses included in the study are “Practical Course in Systematic Review Technique in Clinical Research”, (see course programme in appendix 1) and “Getting started: Writing your first manuscript for publication” [17] (see course programme in appendix 2). The two courses both have 12 seats and last either three or three and a half days resulting in 2.2 and 2.6 ECTS credits, respectively. They are offered by the PhD School of the Faculty of Health and Medical Sciences, University of Copenhagen. Both courses are available and covered by the annual tuition fee for all PhD students enrolled at a Danish university.

### Eligibility criteria

Inclusion criteria for participants: All PhD students enrolled on the PhD courses participate after informed consent: “Practical Course in Systematic Review Technique in Clinical Research” and “Getting started: Writing your first manuscript for publication” at the PhD School of the Faculty of Health and Medical Sciences, University of Copenhagen, Denmark.

Exclusion criteria for participants: Declining to participate and withdrawal of informed consent.

### Informed consent

The PhD students at the PhD School at the Faculty of Health Sciences, University of Copenhagen participate after informed consent, taken by the daily project leader, allowing evaluation data from the course to be used after pseudo-anonymization in the project. They are informed in a welcome letter approximately three weeks prior to the course and again in the introduction the first course day. They register their consent on the first course day (Appendix 3). Declining to participate in the project does not influence their participation in the course.

### Interventions

Online course settings will be compared to onsite course settings. We test if the onsite setting is different to online. Online learning is increasing but onsite learning is still the preferred educational setting in a medical context. In this case onsite learning represents “usual care”. The online course setting is meetings in Zoom using the technicalities available such as chat and breakout rooms. The onsite setting is the learning facilities, at the Parker Institute, Bispebjerg and Frederiksberg Hospital, The Capital Region, University of Copenhagen, Denmark.

The course settings are not expected to harm the participants, but should a request be made to discontinue the course or change setting this will be met, and the participant taken out of the study. Course participants are allowed to take part in relevant concomitant courses or other interventions during the trial.

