### Primary outcome

The primary outcome is short term learning (Kirkpatrick level 2).

Learning is assessed by a Multiple-Choice Questionnaire (MCQ) developed prior to the RCT specifically for this setting (Appendix 4). First the lecturers of the two courses were contacted and asked to provide five multiple choice questions presented as a stem with three answer options; one correct answer and two distractors. The questions should be related to core elements of their teaching under the heading of research training. The questions were set up to test the cognition of the students at the levels of "Knows" or "Knows how" according to Miller's Pyramid of Competence and not their behaviour [21]. Six of the course lecturers responded and out of this material all the questions which covered curriculum of both courses were selected. It was tested on 10 PhD students and within the lecturer group, revised after an item analysis and English language revised. The MCQ ended up containing 25 questions. The MCQ is filled in at baseline and repeated at the end of the course. The primary outcomes based on the MCQ is estimated as the score of learning calculated as number of correct answers out of 25 after the course. A decrease of points of the MCQ in the intervention groups denotes a deterioration of learning. In the MCQ the minimum score is 0 and 25 is maximum, where 19 indicates passing the course.

Furthermore, as secondary outcome, this outcome measurement will be categorized as binary outcome to determine passed/failed of the course defined by 75% (19/25) correct answers.

The learning score will be computed on group and individual level and compared regarding continued outcomes by the Mann–Whitney test comparing the learning score of the online and onsite groups. Regarding the binomial outcome of learning (passed/failed) data will be analysed by the Fisher’s exact test on an intention-to-treat basis between the online and onsite. The results will be presented as median and range and as mean and standard deviations, for possible future use in meta-analyses.

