### Statistical methods

Data is anonymized and blinded before the analyses. Analyses are performed by a researcher not otherwise involved in the inclusion or randomization, data collection or handling. All statistical tests will be testing the null hypotheses assuming the two arms of the trial being equal based on corresponding estimates. Analysis of primary outcome on short-term learning will be started once all data has been collected for all individuals in the last included course. Analyses of long-term academic achievement will be started at end of follow-up.

Baseline characteristics including both course- and individual level information will be presented. Table 2 presents the available data on baseline.

**Table 2 Tab2:** Baseline patient characteristics of participants

VARIABLES AT COURSE LEVEL		
	Name	Practical Course in Systematic Review Technique in Clinical Research; Getting started: Writing your first manuscript for publication
	Setting	Online; Onsite
	Language	Danish; English
VARIABLES AT INDIVIDUAL LEVEL		
	Sex	Male; Female
	Education prior to PhD study	MD; MSc Public Health; University College + MSc; MSc Other
	Pre-test knowledge scores	0-25

We will use multivariate analysis for identification of the most important predictors (motivation, self-efficacy, sex, educational background, and knowledge) for best effect on short and long term. The results will be presented as risk ratio (RR) with 95% confidence interval (CI). The results will be considered significant if CI does not include the value one.

All data processing and analyses were conducted using R statistical software version 4.1.0, 2021–05-18 (R Foundation for Statistical Computing, Vienna, Austria).

If possible, all analysis will be performed for “Practical Course in Systematic Review Technique in Clinical Research” and for “Getting started: Writing your first manuscript for publication” separately.

Primary analyses will be handled with the intention-to-treat approach. The analyses will include all individuals with valid data regardless of they did attend the complete course. Missing data will be handled with multiple imputation [28]*.*

Upon reasonable request, public assess will be granted to protocol, datasets analysed during the current study, and statistical code Table 3.

**Table 3 Tab3:** Outcome framework, measurements and analyses

**Kirkpatrick**	**Term**	**Outcome**	**Tool**	**Measurement**	**Analysis**
Primary outcome					

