### Oversight, monitoring, and adverse events

This project is coordinated in collaboration between the WHO CC (DEN-62) at the Parker Institute, CAMES, and the PhD School at the Faculty of Health and Medical Sciences, University of Copenhagen. The project leader runs the day-to-day support of the trial. The steering committee of the trial includes principal investigators from WHO CC (DEN-62) and CAMES and the project leader and meets approximately three times a year.

Data monitoring is done on a daily basis by the project leader and controlled by an external independent researcher.

An adverse event is “a harmful and negative outcome that happens when a patient has been provided with medical care” [29]. Since this trial does not involve patients in medical care, we do not expect adverse events. If participants decline taking part in the course after receiving the information of the course setting, information on reason for declining is sought obtained. If the reason is the setting this can be considered an unintended effect. Information of unintended effects of the online setting (the intervention) will be recorded. Participants are encouraged to contact the project leader with any response to the course in general both during and after the course.

The trial description has been sent to the Scientific Ethical Committee of the Capital Region of Denmark (VEK) (21041907), which assessed it as not necessary to notify and that it could proceed without permission from VEK according to the Danish law and regulation of scientific research. The trial is registered with the Danish Data Protection Agency (Privacy) (P-2022–158). Important protocol modification will be communicated to relevant parties as well as VEK, the Joint Regional Information Security and Clinicaltrials.gov within an as short timeframe as possible.

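### Removing students who leave the course or change setting contradicts the planned intention-to-treat analysis and the stated exclusions

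*Protocol article*

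**What the plan says.** Four sections of the protocol article bear on a student who consents and then stops the course or moves to the other setting.

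- Interventions: "should a request be made to discontinue the course or change setting this will be met, and the participant taken out of the study".
- Statistical methods: "Primary analyses will be handled with the intention-to-treat approach", followed by "The analyses will include all individuals with valid data regardless of they did attend the complete course" and "Missing data will be handled with multiple imputation".
- Primary outcome, on pass/fail: "data will be analysed by the Fisher’s exact test on an intention-to-treat basis between the online and onsite".
- Eligibility criteria: "Exclusion criteria for participants: Declining to participate and withdrawal of informed consent". Stopping or switching is not listed.

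The section on oversight, monitoring and adverse events adds, about students who decline the course once they know the setting: "If the reason is the setting this can be considered an unintended effect". No section says that a student removed under Interventions stays in the analysis of the randomized arm, and none separates leaving the course from withdrawing consent to the use of data.

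**The concern.** A consenting student who asks to stop on the second day is out of the study under one section and in the primary analysis under another. An analysis plan cannot apply both rules, and end-of-course data that were never requested because the student had been removed cannot be recovered later.

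The removal happens after allocation. A request to change setting is by its nature a response to the setting, so the rate and type of removals may differ between arms. If those removed differ in outcome from those who stay, the comparison is no longer protected by randomization. Enrolling more courses would not cure that.

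Data are also lost that could be had without full attendance. The short-term outcomes are collected on an online form. Academic achievement is read from Google Scholar profiles for 24 months. Preference is a secondary outcome, and a student who asks to switch has a view on exactly that question but would be removed before it is asked.

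**Working it through.** **Comparing the rules for one student who consents and then stops or switches**

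| Section | Consequence |
|---|---|
| Interventions | Removed from the study |
| Eligibility criteria | Not excluded unless consent is withdrawn |
| Primary outcome (pass/fail) | Analysed by intention to treat |
| Statistical methods | Analysed despite incomplete attendance; missing values imputed |

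The first row conflicts with the other three. That finding needs no arithmetic. The calculation below only indicates scale.

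**Inputs from Sample size:** target difference 5 points, SD 10, ICC 0.02, power 80%, two-sided alpha 5%, 12 seats per course, 8 courses per arm required and 10 planned, dropout up to 2 per course.

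**Reproducing the plan's own figure.** The design effect is 1 + 11 × 0.02 = 1.22. With k courses of 12 per arm and t quantiles on 2(k − 1) degrees of freedom,

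k = 2 × 10² × 1.22 × (t₀.₉₇₅ + t₀.₈₀)² / (5² × 12).

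This settles at k = 7.47 (quantiles 2.161 and 0.870), which rounds up to 8 per arm, as stated.

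**Detectable difference with 10 courses of 10 completers per arm**

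- Design effect: 1 + 9 × 0.02 = 1.18.
- Standard error at SD 10: 10 × √(2 × 1.18 / 100) = 1.536.
- t quantiles on 18 degrees of freedom: 2.101 + 0.862 = 2.963.
- Detectable difference: 1.536 × 2.963 = 4.55, about 4.6 points.
- If the SD were 3 (an assumption, not in the protocol): 0.461 × 2.963 = 1.37 points.

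**Shift in one arm's mean.** If a share d is removed and those students would have scored g points below those retained, the mean of those retained exceeds the full-arm mean by d × g. The protocol gives neither d nor g, so both are assumed, with removal in one arm only.

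| d | g | Shift (points) | Share of 4.55 (SD 10) | Share of 1.37 (SD 3) |
|---|---|---|---|---|
| 1/12 | 3 | 0.25 | 5% | 18% |
| 2/12 | 5 | 0.83 | 18% | 61% |
| any | 0 | 0 | 0% | 0% |

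**A second parametrization, at SD 10.** Let the deficit be s SDs below the mean of the whole arm. The shift is d × s × 10 / (1 − d).

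- d = 0.05, s = 0.5: 0.26 points, 5% of the 5-point target.
- d = 0.17, s = 1.0: 2.05 points, 41% of the target.

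**Power is not the issue.** With 10 courses per arm at the protocol's inputs, t-based power is 0.91 with 12 students analysed per course and 0.87 with 10.

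**The case against.** The strongest reply is that the conflict is a matter of wording with little practical reach. The removal rule concerns only students who make a request, and ordinary partial attendance is already covered under Statistical methods. The protocol expects equal adherence because the course carries ECTS credit, and it expects high retention because data are collected at the start and end of the course. Being taken out of the study might also mean only that data collection stops and imputation takes over. The point about limited reach stands as a limit on size. The last reading is possible, but the text does not say it, and it would still discard data that could be collected.

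Several stronger readings are tempting and not supported.

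- A reader might infer that the rule deletes students who do badly, mostly online, and so flatters the online arm. The protocol raises screen fatigue as possibly favouring onsite, but it never links fatigue to leaving. Requests could come from either arm for any reason.
- A reader might take the 18 to 61% column as the finding. It needs an SD of 3, whereas the protocol uses 10. Both columns also apply up to the full any-cause dropout allowance to one arm and none to the other.
- A reader might see three competing analysis sets under Statistical methods. Keeping partial attenders and imputing missing values can be read together. The reference to valid data is loose, but the real conflict is two-way.
- A reader might add that students learn the setting weeks before the first day and "They register their consent on the first course day". That concerns who enters the trial, which is a separate question. The protocol does ask for and record reasons when students withdraw after learning the setting, although it has no outcome scores for them.

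**Conclusion.** The contradiction holds: the removal rule under Interventions cannot stand beside the intention-to-treat analysis and the stated exclusions. Following it creates an exclusion after randomization that can depend on the setting and throws away obtainable data. Confidence is high on the inconsistency and low on its effect. No removal rate, and no outcome for those removed, is documented, so neither direction nor size of bias is known. The illustrative range of 0.25 to 0.83 points rests on one-arm removal of 1 to 2 of 12 and a deficit of 3 to 5 points, and it falls to zero if those removed resemble the rest.

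**What to change.** Reconcile Interventions, Eligibility criteria, Primary outcome and Statistical methods on these lines:

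1. Leaving the course or changing setting does not end study participation. Only withdrawal of consent ends the use of data.
2. Such students are asked to complete the end-of-course online forms and stay in Google Scholar follow-up.
3. They are analysed in the setting to which their course was randomized, with missing scores multiply imputed as already planned. The imputation model can be left to the analysis plan.
4. Removals already made are reported by arm.

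The cost is protocol wording, one e-form sent to leavers, and a few imputed values. Recruitment was due to finish in April 2024, so the request for end-of-course forms may reach few courses. The analysis rule, the long-term follow-up to April 2026 and the reporting by arm can still be put right.
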